**Primary outcome measures**						

Pain score (WOMAC*)	x		x	x	x	x

Pain Score (NRS**)	x	x	x	x	x	x

**Secondary outcome measures**						

Function score (WOMAC)	x		x	x	x	x

Stiffness score (WOMAC)	x		x	x	x	x

HOOS***	x		x	x	x	x

Quality of life (EuroQol EQ-5D)	x		x	x	x	x

Constant and intermittent pain (ICOAP^#^)	x		x	x	x	x

Use of medication	x	x	x	x	x	x

Medical consumption	x		x	x	x	x

Adverse reactions			x	x	x	x

Perceived recovery			x	x	x	x

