**Methods/Design:**

This is a double-blinded, randomized controlled trial. A total of 135 patients (aged > 40 years) with hip osteoarthritis and persistent pain despite oral analgesics visiting a general practitioner or orthopaedic surgeon will be included. They will be randomized to a gluteal intramuscular corticosteroid injection or a gluteal intramuscular placebo (saline) injection. The randomization will be stratified for setting (general practitioner and outpatient clinics of department of orthopaedics). Treatment effect will be evaluated by questionnaires at 2, 4, 6, and 12 weeks follow-up and a physical examination at 12 weeks. Primary outcome is severity of hip pain reported by the patients at 2-week follow-up. Statistical analyses will be based on the intention-to-treat principle.

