### Secondary objectives

The study will assess the effectiveness of an IM gluteal corticosteroid injection versus an IM gluteal placebo injection in patients with hip OA with regard to function, mobility and patients' perceived improvement. Adverse reactions will be registered and an explorative subgroup analysis will be performed stratified for setting (general practitioner and outpatient clinics of department of orthopaedics).

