### Outcomes

#### Questionnaires at baseline, 2, 4, 6 and 12 weeks

All outcomes are measured at baseline and at 2, 4, 6 and 12 weeks follow-up. The primary outcome is severity of hip pain reported by the patient at 2 weeks. This will be measured with two validated questionnaires: an 11-point numerical rating scale (NRS) in rest and on walking (0-10, where 0 equals no pain) [12], and the Western Ontario and McMaster University Osteoarthritis Index (WOMAC) pain subscale [13]. The WOMAC pain subscale will be converted to a 0-100 score, where 0 equals no symptoms. The WOMAC is recommended by the Osteoarthritis Research Society for use in clinical trials in patients with hip OA to measure pain and disability [13].

Secondary outcomes include the primary outcomes at 4, 6, and 12 weeks follow-up. Additional secondary outcomes are the disease-specific WOMAC function and stiffness subscales [13]. Both the function and stiffness subscale of the WOMAC will be converted to a 0-100 score. Data on pain and function will also be obtained with the Hip disability and Osteoarthritis Outcome Score (HOOS) [14], which was developed as an extended version of the WOMAC to evaluate the whole domain of patient-relevant outcome in young and active patients and is validated in the Dutch language [15].

For patients' perceived recovery a 7-point Likert scale will be used (score range 1 = 'worse than ever' to 7 = 'major improvement') [9,16]. Quality of life will be measured with the Euroqol (EQ-5D) [17]. Constant and intermittent pain will be obtained with the questionnaire Intermittent and Constant Osteoarthritis Pain (ICOAP) taking into account both pain intensity and impact on quality of life [18]. Patients' medical consumption will be registered and adverse reactions noted [9,16]. For this, a questionnaire will be used that covers the known local and systemic adverse reactions to corticosteroids. Data on daily pain and pain medication use will be obtained with a diary during the first 2-weeks follow-up.

Another secondary outcome is the difference in percentage of responders as defined by the OMERACT-OARSI (improvement in at least 2 of the 3 following domains: ≥20% improvement in WOMAC pain, ≥20% improvement in WOMAC function, or markedly improved on the patients' global assessment) [17].

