At baseline various patient characteristics (gender, age, height, weight, race, education, marital status, occupational situation and co-morbidities) are recorded. Table 2 presents an overview of the parameters measured during follow-up.

**Table 2 T2:** Timing of measurements and outline of primary and secondary outcome measures

	Baseline	Daily diary for 2 weeks	2 weeks	4 weeks	6 weeks	12 weeks

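### Adverse reactions are asked about at weeks 2, 4, 6 and 12 but not at baseline, so complaints already present may inflate the rates in each arm

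*Protocol article*

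**What the plan says.** The Outcomes section opens with a general rule: "All outcomes are measured at baseline and at 2, 4, 6 and 12 weeks follow-up". The same section counts adverse reactions among the things collected ("Patients' medical consumption will be registered and adverse reactions noted") and describes the instrument: "a questionnaire will be used that covers the known local and systemic adverse reactions to corticosteroids". The secondary objectives state that "Adverse reactions will be registered".

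Table 2 places adverse reactions under the secondary outcome measures, with marks at the four follow-up times and blanks under baseline and the diary: "Adverse reactions x x x x". One other secondary outcome has the same pattern: "Perceived recovery x x x x". All the remaining secondary outcomes have a baseline mark.

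The baseline records that bear on earlier health are the patient characteristics, which end with co-morbidities ("education, marital status, occupational situation and co-morbidities) are recorded"), and the Table 2 rows for use of medication and medical consumption. No baseline symptom list is described.

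**The concern.** A reaction to an injection cannot precede it, but the complaint that a patient reports can. The patients are over 40, have had symptomatic hip disease for at least 6 months and have pain despite oral medication. Some may already have complaints that also appear among the known effects of corticosteroids. If such a complaint is reported at week 2, nothing described for baseline shows whether it is new, worse or unchanged. A co-morbidity record lists conditions, not symptoms, so it answers this only in part.

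Two things are at stake. The rates reported for each arm may be too high as a description of what follows the injection. The difference between arms may also be estimated with more noise than necessary, which makes a real excess easier to miss. The missing information cannot be collected properly once a patient has been injected, and the abstract says that recruitment has started.

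**Working it through.** **The two statements side by side.** The Outcomes sentence implies five measurement times for every outcome: baseline and four follow-ups. Table 2 gives adverse reactions and perceived recovery four. The two conflict for both rows, but the rows differ in kind. Perceived recovery asks about change, so a baseline value has no meaning. A list of complaints can be completed before the injection, and only the causal label has to wait.

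**The plan's own figure.** With a difference of 10, an SD of 20, two-sided 5% alpha (sidedness is not stated) and 80% power, n per group = 2 × (1.960 + 0.842)² × (20/10)² = 62.8, so 63 by the normal approximation. The t-test version gives 63.8, so 64 as stated. Then 128 / 0.95 = 134.7, so 135. The sample size reproduces and is not affected by this point. It supplies only the 64 per arm used below.

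**Illustration of size. All symptom rates are assumptions.** Let b be the share of patients with a listed complaint before the injection, and let c (placebo) and t (active) be the rates of new onset among the rest. Assume that every pre-existing complaint is reported again at follow-up.

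- All complaints counted: p = b + (1 − b)c versus b + (1 − b)t.
- New onset only, over all 64: p = (1 − b)c versus (1 − b)t.
- The difference is (1 − b)(t − c) in both cases. Only the variance changes.
- SE = √[p₀(1 − p₀)/64 + p₁(1 − p₁)/64]; half-width = 1.96 × SE; power ≈ Φ(difference/SE − 1.96).

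For b = 30%, c = 5%, t = 20%:

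- All complaints: 0.30 + 0.70 × 0.05 = 33.5% versus 0.30 + 0.70 × 0.20 = 44.0%. Difference 10.5 points, SE 8.56, half-width 16.8, power 23%.
- New onset only: 3.5% versus 14.0%. Difference 10.5 points, SE 4.91, half-width 9.6, power 57%.

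Over a range of backgrounds and for a smaller effect:

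| b | c versus t | Difference (points) | Power, all complaints | Power, new onset only |
|---|---|---|---|---|
| 10% | 5% versus 20% | 13.5 | 47% | 70% |
| 20% | 5% versus 20% | 12.0 | 32% | 64% |
| 30% | 5% versus 20% | 10.5 | 23% | 57% |
| 30% | 5% versus 10% | 3.5 | 6% | 14% |

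At 3.5% of 64, about two events, the normal approximation is optimistic. Fisher's exact test gives about 44% instead of 57% for new onset, and about 19% instead of 23% for all complaints.

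**The case against.** The strongest reply is that the conflict is loose wording. The Outcomes sentence is a general opening and Table 2 is the item-by-item schedule. Perceived recovery has the same blank cell, and an adverse reaction to an injection has no baseline value. This stands in part. Table 2 is clearly what the authors intend, and the inconsistency alone would be editorial. It does not explain how a complaint already present would be recognised.

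The design also limits the harm. Patients are randomised to corticosteroid or saline ("They will be randomized to a gluteal intramuscular corticosteroid injection or a gluteal intramuscular placebo (saline) injection") under double blinding, so background complaints are expected equally in both arms and favour neither. This stands in full. The trial is sized for pain, not for testing adverse reactions, and the objective promises only that they are registered.

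The illustration rests on assumed rates and on every pre-existing complaint being reported again. If the items ask about complaints that began after the injection, the effect would be smaller. The article does not show the wording, so this can be neither confirmed nor excluded.

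A reader might also infer three stronger claims, none of which the document supports:

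- That the questionnaire is restricted to known corticosteroid reactions. The text says that it covers them, which does not exclude other content.
- That events outside the list have nowhere to be recorded. That is inferred from silence. An open item or separate adverse-event reporting is the kind of detail a condensed article leaves to the full protocol.
- That pre-existing complaints will be counted as reactions. No rule says so. It is a risk left open by the schedule.

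**Conclusion.** The point holds as a minor but worthwhile improvement to a secondary safety objective. The schedule omits a baseline administration of the adverse-reaction questionnaire, in literal conflict with the Outcomes sentence, and no described baseline record fills the gap. The between-arm comparison stays unbiased. The exposure is inflated rates within each arm and a less precise contrast.

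The size cannot be fixed from the document. In the assumed cases with a large effect (5% versus 20% new onset), counting only new complaints adds 23 to 34 percentage points of power as background goes from 10% to 30%. With 5% versus 10% and 30% background it adds about 8, and power remains low either way. The direction follows from the model: the difference is the same and the variance is larger when all complaints are counted. It requires that pre-existing complaints are in fact reported at follow-up. The primary outcome and the sample size are untouched.

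**What to change.** 1. Give the same symptom list once in the existing baseline questionnaire, before the injection, and add the baseline mark to the adverse-reactions row of Table 2, labelled as pre-injection complaints.
2. State that complaints which are new or worse than baseline are reported by arm.
3. Qualify the general sentence in the Outcomes section so that perceived recovery is measured at follow-up only.

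The cost is a few minutes of patient time at baseline. Patients already injected will have no baseline list, so the report should say how many there are and show their complaints without the new-or-worse classification. If the list is not added, the sentence should at least be brought into line with Table 2, with a statement of how complaints present before the injection are classified.

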**Others**						

Demographic data	x					

Co-morbidity	x					

Physical examination hip, knee and lumbar spine	x					x

Laboratory assessment (ESR^##^, Hs-CRP^###^)	x					

* *WOMAC *Western Ontario and McMaster University Osteoarthritis Index

** *NRS *Numerical Rating Score

*** *HOOS *Hip disability and Osteoarthritis Outcome Score

^# ^*ICOAP *Intermittent and Constant Osteoarthritis Pain

^## ^*ESR *Erythrocyte Sedimentation Rate

^### ^*Hs-CRP *high sensitive C-reactive protein

#### Physical examination at baseline and 12-weeks follow-up

Both hip joints will be examined for presence of groin pain or peri-trochanteric pain at palpation, range of motion and pain at/during movement for flexion/extension, abduction, and for internal/external rotation. Hip rotations will be examined in sitting position with the hips and knees in 90°. Hip flexion/extension and abduction will be examined in supine position. A goniometer will be used to measure degrees of range of motion [19].

To gain insight in knee and lumbar spine co-morbidity both knee joints and lumbar spine will be examined. Pain at palpation of the medial or lateral joint space of the knee, hydrops and range of motion of flexion/extension of the knee will be registered. Pain at palpation of the spinous processes or sacro-iliac joints and lateroflexion and flexion of the lower spine (fingertip-floor distance and classic Schober test) will be examined [20].

#### Laboratory assessment

At baseline, two blood samples (9 ml) will be collected. One to measure the erythocyte sedimentation rate, which is used for the American College of Rheumatology criteria of hip OA [21]. The other for high-sensitive C-reactive protein (hs-CRP) to gain insight in the inflammatory processes. The samples will be analysed at the Trial Laboratory Department of the Erasmus MC.

### Sample size

Data from the Qvistgaard et al. study (patients with hip OA from primary care and secondary care) were used to calculate our sample size [6]. That study showed a baseline standard deviation (SD) of 20 for pain at rest and at walking (0-100 visual analogue scale; VAS). Assuming a minimal clinically relevant difference of 10 points (effect size 0.5), 64 patients per group will be needed to show a statistically significantly difference using 80% power and with a 5% alpha.

In that same study [6] the WOMAC total score (0-96) was used with an SD of 15. Standardized to a 0-100 score this SD is almost 16. Assuming an SD of 16 and an 8-point difference as clinically relevant (effect size 0.5), the same sample size is needed.

We checked these scores in a Dutch study population with hip OA, i.e. those with a K-L score of the hip ≥ 2 and a VAS pain score ≥ 30, participating in the GOAL study [22]. This showed they had a mean VAS score of 56.4 with an SD of 19.3, a mean WOMAC pain score of 51.2 with a SD of 16.4; these data are very similar to the SDs in the study of Qvistgaard et al. Therefore, in the planned trial, we will include 135 patients, anticipating only 5% loss to follow-up based on the relatively short follow-up and earlier experience with loss to follow-up [22,23].

### Data analyses

Data analysis will be performed based on the 'intention to treat' principle.

Descriptive statistics will be used to describe patient's characteristics, items of physical examination, and the severity of radiologic hip OA.

Linear mixed models will be used for repeated measures to analyze the continuous outcome measures. Fixed effects will be time, time by therapy and the covariates we adjust for. For patients lost to follow-up, we will include all observed data in the analysis. Adjustment will be made for those baseline variables that change the effect estimate by more than 10%. Similar analyses with Generalized Estimating Equations techniques for repeated measures will be done for dichotomous outcome measures.

Subgroup analyses for setting will be analyzed by assessing interaction effects between type of intervention and setting on the primary outcomes; in addition, the estimates will be shown for both settings separately. We realize that these subgroup analyses will remain solely explorative because our sample size is not directed to powerful subgroup analyses.

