### Randomisation

An independent pharmacy assistant will allocate each patient based on computerized randomization lists to either receive placebo (saline) injection or triamcinolone acetate 40 mg injection IM. Randomization is stratified for setting (general practitioner and outpatient clinics of department of orthopaedics) and uses random blocks of 2 and 4.

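### Baseline pain is not fixed in the primary model, and the 10% change-in-estimate rule can drop it: always including it costs nothing and recovers about 1 to 2 power points on average

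*Protocol article*

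**What the plan says.** In the protocol article, Data analyses, continuous outcomes go into a linear mixed model for repeated measures: "Fixed effects will be time, time by therapy and the covariates we adjust for". A single rule decides which covariates those are: "Adjustment will be made for those baseline variables that change the effect estimate by more than 10" per cent. Baseline pain is not named as a covariate, and the section does not say whether the baseline visit is one of the levels of time.

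The data needed are collected. Under Outcomes: "All outcomes are measured at baseline and at 2, 4, 6 and 12 weeks follow-up". Table 2 confirms a baseline value for WOMAC pain and for NRS pain, the primary scales.

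The Sample size section uses an unadjusted SD: "That study showed a baseline standard deviation (SD) of 20 for pain at rest and at walking (0-100 visual analogue scale; VAS"). It then states: "Assuming a minimal clinically relevant difference of 10 points (effect size 0.5), 64 patients per group will be needed", "using 80% power and with a 5% alpha". For WOMAC: "Assuming an SD of 16 and an 8-point difference as clinically relevant (effect size 0.5), the same sample size is needed".

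**The concern.** A change-in-estimate rule is a tool for finding confounders. In a randomised trial a baseline variable moves the estimate only as far as chance has left it unbalanced between the arms. Adjusting for a prognostic variable, however, reduces the residual variance by a factor of 1 − r² whether or not the arms are balanced. The rule therefore tends to discard baseline pain when the arms happen to be balanced, and the standard error is then larger than the data require. It also lets the observed data decide whether the primary analysis is adjusted for baseline. At stake are the width of the confidence interval for the primary effect and some power.

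**Working it through.** **Inputs.** From Sample size: difference 10 points, SD 20 (0–100 scale), 80% power, 5% alpha, 64 per group, 5% loss. Alpha is taken as two-sided, because that reproduces the stated size. Allocation is taken as 1:1, from the equal group sizes and from Randomisation, which "uses random blocks of 2 and 4". From Data analyses: the 10% rule. Not in the article: the correlation r between baseline and week-2 pain, assumed to be 0.3, 0.5 or 0.7.

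**Step 1: the plan's own figure.** Effect size = 10/20 = 0.5. A two-sided t-test at 80% power needs 63.8, so 64 per group. Then 128/0.95 = 134.7, so 135. WOMAC has 8/16 = 0.5 and the same answer. Power at 64 per group is 80.1%. Both stated figures reproduce, with no credit taken for baseline adjustment.

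**Step 2: always adjusting.** Residual SD = 20√(1 − r²), which is 19.1, 17.3 or 14.3. The 95% CI half-width is 1.98 × 20 × √((1 − r²) × 2/64). With no adjustment it is 7.0 points. With adjustment it is 6.7, 6.1 or 5.0.

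**Step 3: the rule as written.** Simulated trials had 64 per arm, one week-2 outcome, one baseline covariate and a true effect of 0.5 SD. Baseline entered only if |adjusted − unadjusted| > 0.1 × |unadjusted|.

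| Assumed r | 0.3 | 0.5 | 0.7 |
|---|---|---|---|
| Trials in which baseline pain is dropped | 64% | 43% | 31% |
| Excess standard error in those trials | 4% | 15% | 39% |
| Power, 10% rule | 82.6% | 87.8% | 95.5% |
| Power, always adjusting | 83.4% | 89.6% | 97.3% |
| Loss (points) | 0.8 | 1.8 | 1.8 |
| Mean half-width, 10% rule | 6.9 | 6.5 | 5.6 |
| Half-width, always adjusting | 6.7 | 6.1 | 5.0 |

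The excess standard error comes from the mean standard errors in SD units: 0.1764/0.1689 = 1.044, 0.1764/0.1533 = 1.151 and 0.1765/0.1266 = 1.394. The mean half-width under the rule can be checked as a mixture. At r = 0.5, 0.43 × 7.0 + 0.57 × 6.1 = 6.5.

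**Step 4: does the repeated-measures structure already use baseline?** Suppose baseline is a level of categorical time, with five visits and complete data. Time plus time by therapy, without a therapy main effect, still fits a separate treatment difference at every visit, baseline included. The generalised least squares variance of the week-2 contrast is then 0.03125 in SD² units at every r, which equals 2/64, the variance of the raw difference. Only if the baseline-by-therapy term is removed does it fall to (1 − r²) × 2/64 = 0.0284, 0.0234 or 0.0159, the same as analysis of covariance.

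**The case against.** **The model may already be a constrained longitudinal one.** The listed terms omit a therapy main effect, and the outcomes include a baseline visit. If the authors mean that the arms share a baseline mean, baseline pain is fully used and nothing is lost. This is a fair possibility, but step 4 shows that with categorical time it needs an explicit constraint, and the section states none. The objection leaves an ambiguity that the fix would settle.

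**The average loss is small.** This stands. The threshold is relative to the estimate, so baseline is dropped more readily when the observed effect is large, and those trials tend to reach significance anyway. At r = 0.5, power among the trials that drop baseline is 90.6% unadjusted, against 94.5% had it been kept. A reader might infer that power stays near 80% when it could be about 90%. That compares always adjusting with never adjusting, and the plan is not never to adjust: at r = 0.5 baseline would enter in about 57% of trials.

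**The trial meets its stated power.** This also stands. A reader might infer that the trial is underpowered. It is not, since 64 per group was computed on the raw SD and any gain from baseline comes on top of 80%.

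**No bias or false-positive problem is shown.** For this one covariate, simulated type I error under the rule was 4.8%, 4.4% and 4.2%. A baseline variable that is left out shifts the estimate by at most 10% by construction, and the mean shift was about 0.5 points on the 0–100 scale. Leftover imbalance is therefore not a strong argument.

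**A fuller analysis plan may exist.** It may, but the article is not silent here. It states a selection rule that, as written, covers baseline pain.

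**Conclusion.** The concern holds as a matter of efficiency. The stated rule can exclude baseline pain on grounds unrelated to its value as a predictor, and excluding it brings no benefit. On average the cost is about 1 to 2 power points and up to about 0.6 points of CI half-width on a 0–100 scale (5.6 against 5.0 at r = 0.7). In the particular trials where baseline is dropped, the standard error is 4% to 39% too large, depending on r. These sizes rest on the assumed correlations, on 64 per arm at the planned effect, and on a simulation of one covariate at one visit. They do not apply if the authors intended a model with a common baseline mean.

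**What to change.** Add a sentence to Data analyses: for each primary pain score (NRS at rest, NRS on walking, WOMAC pain) and every other continuous outcome measured at baseline, the baseline value of the outcome being analysed is always in the model. It enters either as a covariate or as a baseline response with the group means constrained equal (no baseline-by-therapy term). State which form is used, and say that the 10% rule does not apply to this variable.

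The cost is one sentence and, in the covariate form, one degree of freedom. No extra patients or measurements are needed, and the sample size can stay as it is.

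### The 10% change-in-estimate rule makes the primary model's covariates depend on the observed treatment effect; the harm is modest and the remedy is to fix them in advance

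*Protocol article*

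**What the plan says.** The Data analyses section of the protocol article gives one model for the continuous outcomes, a linear mixed model for repeated measures: "Fixed effects will be time, time by therapy and the covariates we adjust for". Which covariates those are is settled by a single rule: "Adjustment will be made for those baseline variables that change the effect estimate by more than 10" per cent. No covariate is named as always included, and no unadjusted or fixed-covariate model is named as primary. Dichotomous outcomes follow the same pattern: "Similar analyses with Generalized Estimating Equations techniques for repeated measures will be done for dichotomous outcome measures".

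The outcome section sets the primary endpoint: "The primary outcome is severity of hip pain reported by the patient at 2 weeks". It also lists what is recorded at entry: "At baseline various patient characteristics (gender, age, height, weight, race, education, marital status, occupational situation and co-morbidities) are recorded". Under Randomisation, setting (general practice or orthopaedic clinic) is the stratification factor, with random blocks of 2 and 4. In the analysis section setting appears only in the explorative subgroup analysis.

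**The concern.** Change-in-estimate is a tool for choosing confounders in observational data. In a randomised trial baseline differences are due to chance, and the reason to adjust is prognostic strength known beforehand. The rule here uses a different criterion. The treatment effect must be estimated before the model is known, and the threshold is a percentage of that same effect. A covariate that shifts the estimate by 1 point passes easily when the crude effect is 2 points and is on the boundary when it is 10.

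Two things are at stake. Strong prognostic covariates may be dropped when the effect is as large as the design assumes, which wastes precision. And the model's standard error takes the chosen covariates as given, so it need not match the sampling variability of the whole procedure.

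**Working it through.** **1. The plan's own figure.** Inputs from Sample size: "That study showed a baseline standard deviation (SD) of 20 for pain at rest and at walking" and "Assuming a minimal clinically relevant difference of 10 points (effect size 0.5), 64 patients per group will be needed"; 80% power, 5% alpha (taken as two-sided).

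n per group = 2(1.960 + 0.842)² × (20/10)² = 2 × 7.85 × 4 = 62.8, so 63 by the normal approximation. The t-test version gives 63.77, so 64. Total: 128/0.95 = 134.7, so 135. Both stated figures are reproduced. The WOMAC version ("Assuming an SD of 16 and an 8-point difference as clinically relevant (effect size 0.5), the same sample size is needed") has the same standardised effect.

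**2. How often a strong covariate passes.** In linear regression at one visit, adding a covariate moves the estimate by

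shift = (covariate slope) × (difference in covariate means between arms).

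For a standardised covariate the difference in means has SD √(2/64) = 0.177. If its correlation with the outcome is r, the slope is about 20r. Assume r = 0.5: the SD of the shift is 10 × 0.177 = 1.77 points.

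- Estimate of 10 points: threshold 1.0. P(enter) = P(|Z| > 1.0/1.77) = P(|Z| > 0.57) = 0.57, so it is left out in about 43% of trials.
- Estimate of 5 points: threshold 0.5. P(enter) = P(|Z| > 0.28) = 0.78.
- Estimate near 0: the threshold is near 0 and almost any covariate enters.

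The WOMAC figures give the same answer: SD of the shift 0.5 × 16 × 0.177 = 1.41, threshold 0.8, and 0.8/1.41 = 0.57.

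**3. Simulation.** 128 evaluable patients, 1:1, outcome SD 1, linear regression at one visit standing in for the mixed model, 6,000 trials per row. Each candidate was added singly and kept if it moved the crude estimate by more than 10%; the final model held all those kept. The comparator is a fixed model with every candidate. Assumed correlations: set A, one covariate at 0.5; set B, ten at 0.5, 0.3, 0.3, 0.1, 0.1 and five at 0; set C, eight at 0.6, 0.3, 0.2, 0.1 and four at 0.

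| Set | Strongest covariate enters, true effect 0 / 0.25 / 0.5 SD | Mean number entering |
|---|---|---|
| A | 89% / 77% / 57% | – |
| B | 89% / 77% / 57% | 5.1 / 3.5 / 1.6 |
| C | 91% / 80% / 64% | 4.2 / 2.9 / 1.4 |

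With twelve candidates (one at 0.5, four weak, seven noise), about 5.5 enter at true effect 0 and 1.4 at 0.5 SD. The strongest is left out in about 42% of trials at 0.5 SD, in line with step 2.

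**4. Standard error, error rate and power.**

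| Set | Mean reported SE / true SD at 0.5 SD | Type I error, rule (fixed) | Power at 0.5 SD, rule (fixed) | Power at 0.25 SD, rule (fixed) |
|---|---|---|---|---|
| A | 0.1634/0.1577 = 1.04 | 4.0% (4.7%) | 87.2% (89.1%) | 33.7% (36.5%) |
| B | 0.1568/0.1463 = 1.07 | 4.2% (5.2%) | 91.9% (94.6%) | 37.5% (43.8%) |
| C | 0.1498/0.1355 = 1.11 | 3.9% (4.9%) | 94.7% (96.9%) | 41.3% (47.6%) |

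Under the rule, coverage was 95.5 to 96.4% and bias at most about 0.01 SD.

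**5. The same rule without a strong candidate.** With baseline pain outside the pool (four covariates at 0.15, seven at 0), the ratio of reported SE to true SD was 0.98 to 1.00. In a longer check of 40,000 trials at effect 0 the ratio was 0.98 and type I error 5.4%. At effect 0.5 SD (20,000 trials) the ratio was 1.00 and coverage 95.1%.

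**6. Setting.** With blocks of 2 and 4 and one list per setting (assumed), the arms differ by at most 2 patients within a setting. In the worst case the proportion from general practice differs between arms by 2/64 = 0.031. To move a 10-point estimate by 1 point, the two settings would have to differ by 1/0.031 = 32 points on the 0–100 scale. Before losses to follow-up, the rule would therefore rarely admit setting at the design effect.

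**7. Dichotomous outcomes, if a logit link is used.** With responders at 40% v 60%, the marginal odds ratio is (0.6/0.4)/(0.4/0.6) = 2.25. Integrating over a perfectly balanced normal covariate, the conditional odds ratio is higher by 5% at logit SD 0.5, 9% at 0.7, just over 10% near 0.75, and 18% (2.66) at 1.0.

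**The case against.** The strongest reply is that little goes wrong. The rule is an algorithm stated in advance. Applied mechanically, it kept type I error near or below 5%, gave almost no bias, and in all three sets of step 3 had more power at the design effect than the planned 80%. All of this stands, and it limits the size of the point. A reader might infer false-positive inflation, or free post hoc choice of covariates. The calculations do not support the first, and the text does not support the second.

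The standard-error mismatch also depends on baseline pain, or something equally prognostic, being a candidate. The listed fixed effects include no therapy main effect, and the outcomes are measured at baseline too. That is compatible with a mixed model holding baseline as the first repeated measure with a common mean, which already adjusts for baseline pain. The text does not settle this. If that is the model, the mismatch largely disappears (step 5), but the rule still governs every other covariate, including setting.

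It is also tempting to say that the rule fires on balanced covariates for every dichotomous outcome. The article names no link function, and it describes the responder outcome as a difference in percentages, a scale without this problem. The argument holds only for a logit link and a strong covariate, and it concerns secondary outcomes.

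Finally, the candidate list and the outcome and visit at which the 10% is judged are details that an article may leave to the full protocol or SAP. Their absence is not part of this point.

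**Conclusion.** The point holds in a limited form. The stated rule ties the primary model to the observed treatment effect. Strong prognostic covariates can be left out at the design effect (about 42% of simulated trials for r = 0.5, if baseline pain or its equal is a candidate), and the stratification factor is not guaranteed to enter. This is a poorly chosen stated rule, not a missing detail: a fuller plan could cure it only by replacing the rule.

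The consequence is inefficiency rather than invalidity. With a strong candidate in the pool, standard errors are roughly 4 to 10% too large at effect size 0.5. The power loss against a fixed model is about 2 to 3 points there and about 3 to 6 points at half that effect. Without such a candidate the standard errors are about right. These sizes rest on assumed correlations, assumed numbers of candidates and a single-visit linear model. The dependence on the observed effect follows from the rule itself.

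**What to change.** Replace the 10% rule with covariates fixed in advance for the primary model: the baseline value of the outcome (as a covariate or through a mixed model with a constrained common baseline mean), setting, and any prognostic variables named beforehand. Apply the same principle to the dichotomous outcomes, and state the link function. If change-in-estimate adjustment is still wanted, report it only as a sensitivity analysis.

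The cost is one sentence in the plan and somewhat less analysis work. The sample size of 64 per group and 135 in total is unchanged. In the simulated sets the fixed model kept type I error at 4.7 to 5.2%, coverage at about 95%, and power at 89 to 97% for the design effect.
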